**Fig. 3 Fig3:**
[figure not shown]
The fitness dice with interchangeable faces

Teachers will be requested to use the dice on at least eight consecutive PE lessons after they attend the workshop. This length was chosen because it allowed sufficient time for teachers and students to familiarize with the activity, but at the same time not too long to cause disruptions to teachers’ curricula. According to Lonsdale et al. [14], previous school-based PE interventions had a length of 1 to 130 weeks. In particular, fitness infusion interventions last 4 to 24 weeks. Therefore, the length of the SELF-FIT was in line with similar interventions that have been employed previously. An implementation guideline for these eight lessons will be provided to teachers. Specifically, we will recommend teachers spend 20 min using the fitness dice during each of the eight lessons. The first two lessons will be a familiarization session for both teachers and students, and we will recommend teachers use one-to-many instruction format, and utilize one die at a time. Essentially, the teacher will toss the die and instruct students to do the activity shown on the die. After the two familiarization lessons, we will recommend teachers use the dice using a circuit-training format. Essentially, depending on class size, equipment and space availability, two to four stations could be set up, and students will use a specific die for each station. Teachers could instruct students to change stations after a specific time (e.g., 1 min), so students could complete multiple circuits. We will recommend teachers increase student participation in the fitness dice activity throughout the eight-lesson period. For instance, we recommend teachers to nominate activity leaders to demonstrate the selected exercises, select activity cards to be placed in the dice, or design new exercises to be inserted. We will also suggest teachers add other game play elements, such as tossing a die for students at other stations, inserting “wild cards” in the dice faces for self-chosen activities, or adding an additional die to decide the time or repetition of the exercise to complete. Teachers will be told that they do not have to strictly follow these guidelines and they are free to improvise will the aim of encouraging maximal engagement and enjoyment of students.

A pilot study was conducted to specifically test the feasibility of using the fitness dice in a school PE setting. Two teachers from one secondary school were invited to pilot test the fitness dice in their classes (one class each; both were mixed-sex). The aim of conducting the pilot study was to collect preliminary evidence that (1) the use of the fitness dice is practically feasible in real school PE settings, and its implementation would not cause any major drawbacks or problems, (2) students found the activity more interesting compared to traditional fitness activities. To this end, we observed four lessons per class. Within these four lessons, the first two were taught using existing methods and equipment, while the fitness dice were used in the final two classes. All lessons in the pilot study were video-recorded for review purposes. Two teachers and ten students were interviewed after the pilot study. During the interviews, teachers reflected that the use of the fitness dice did not cause any major disruptions or delays in their lessons. Neither teachers nor students felt there were noticeable differences in terms of students’ intensity or volume of physical activity exerted when the fitness dice were used. Students either said they found the fitness dice activity to be more interesting than traditional fitness activities, or they felt there were no differences. No students said they preferred traditional fitness activities over using the fitness dice. The results from the pilot study suggested that the fitness dice may be a viable tool to be used for fitness activities in school PE.

#### Other motivational components

Apart from the main intervention components of need support teaching and the fitness dice, we will also recommend teachers employ other motivational components as part of the intervention. First, to encourage teachers to reflect on and improve their need supportive teaching strategies, we have designed a self-reflection questionnaire for teachers to complete after each lesson. Teachers will be asked to complete the questionnaire, designed based on the SAAFE principles, and reflect if they have adequately utilized supportive behaviors, and avoided controlling ones during that lesson. By completing the self-administered questionnaire, we hope that teachers will be reminded of the SAAFE principles and need supportive strategies, so they can use these to improve their teaching in the following lessons. Secondly, teachers will be requested to play some upbeat music during the fitness dice activity, as the introduction of music to PE may increase students’ activity levels [41]. After the familiarization lessons, teachers can also invite students to choose the music to be played in the following lessons. This may further enhance students’ perceptions of autonomy towards PE. Further, we will provide students with an activity record and goal setting form to be completed after each PE lesson. Specifically, students will be asked to record the exercises they have completed, together with the time or repetition they completed. On the form, they will also be encouraged to set goals for the week after.

### Fidelity of intervention

To ensure intervention fidelity, the content of lessons where accelerometer data are measured will be recorded by trained research assistants. Specifically, using a standardized form, research assistants will record the types of activities (e.g., stretching, ball games, track and field, fitness) during that lesson, as well as the start and end times of each set of activity. At follow-up, research assistant will also record for each activity whether the fitness dice were used and if music was played during the activity period. This will determine if some or all intervention components were implemented in lessons for the experimental group, but not in classes of the control group (i.e., intervention fidelity). At least one lesson per class will be video-recorded for review purposes. We will also ask teachers to report, after the fourth and eighth lesson during the intervention period, if they have completed the self-reflective questionnaires or allowed students to complete the record and goal-setting forms.

### Outcomes

The primary outcome of the randomized controlled trial is the percentage of time students spent in MVPA during PE classes. Secondary outcomes include percentage of time spent in MVPA during leisure time, student perceptions of need support by teachers, basic psychological need satisfaction, autonomous motivation towards PE, intention to engage in physical activity, psychological well-being, and indicators of health-related fitness. Identical measures for all outcomes will be used at both time points. The percentage of time spent in MVPA during PE will be measured using accelerometers, during three randomly selected lessons at each time point. Leisure-time MVPA will be measured once during baseline and follow-up, respectively. Questionnaire-based measures will be collected on one occasion at baseline and follow-up, respectively. Questionnaires will be administered during one of the last two PE classes of the respective time point. All accelerometer and questionnaire data will be collected at schools by research assistants who will be trained by the authors of the current manuscript. To ensure that the information record and data collection procedures will be consistent across all research assistants, they will be accompanied by the project manager during their respective first data collection sessions at schools.

#### Moderate-to-vigorous physical activity

Students’ MVPA will be measured using ActiGraph GT3X+ and wGT3X-BT accelerometers worn at the waist. For the primary outcome of MVPA during PE, measures for three lessons at each time point will be taken. Specifically, trained research assistants will administer the devices to students at the beginning of the lessons, and collect them when the lesson ends. For the secondary outcome of leisure-time MVPA, the same ActiGraph devices will be used, but an 8-day administration protocol will be applied. That is, after the devices are administered to measure students’ MVPA during PE (Day 0), instead of retrieving the accelerometers immediately after the lesson ends, they will be collected 8 days later (Day 8). That will allow data from seven full days (i.e., Days 1 to 7) to be collected if the students wear the devices correctly. Participants will be asked to wear the devices throughout their waking hours within the data collection period, except during water-based activities (e.g., swimming, bathing) or occasions where they are not allowed to wear such devices (e.g., a contact sport match). Leisure-time MVPA will only be measured once during baseline (i.e., the first semester) and follow-up (i.e., the second semester), respectively. It is worth noting that compliance to accelerometers protocols in school-based physical activity interventions targeting adolescents is typically low [42]. In the current study, accelerometer wear-time criteria will be defined as at least three weekdays with >8 h. This is consistent with previous research [43] and is associated with higher levels of compliance in school-based physical activity interventions [42].

Accelerometer-based data will be categorized as sedentary, light, moderate, or vigorous levels using the cutoff points proposed by Evenson et al. [44]. Epoch lengths of 1-s will be used to provide a more accurate representation of students’ activities [45, 46]. The percentages of time students spent in moderate and vigorous activities will be summed as a measure for MVPA. For leisure-time MVPA measures, students’ percentage of time spent in MVPA during weekdays and weekends will be used as secondary outcomes, respectively. Leisure time MVPA data will be considered valid only if students wore the devices on at least three weekdays (for weekday data), or at least one weekend day (for weekend data).

#### Perceived need support by teachers

The Learning Climate Questionnaire [47] will be used to measure students’ perceived need support from teachers (e.g., “I feel that my teacher provides me choices and options”). The short, 6-item version of the scale will be used to reduce the load on participants. English items were translated to Chinese by two individual groups of translators (two per group) using a back-translation protocol. Students will be asked to respond to the scale using a 7-point scale from 1 (*strongly disagree*) to 7 (*strongly agree*). The translated scale was administered to a group of students in a pilot study. The corresponding scale scores had a Cronbach alpha of .87.

#### Basic psychological need satisfaction

The satisfaction of basic psychological needs for competence, autonomy, and relatedness will be measured using an adapted version of the Basic Needs Satisfaction in Sport Scale [48]. The 20-item scale was originally developed to measure satisfaction of competence (e.g., “I am skilled”), autonomy (e.g., “I feel I participate in PE activities willingly”), and relatedness (e.g., “There are people who I can trust”) in a sport context, and was simultaneously developed in both English and Chinese. The Chinese version of the scale will be used. Item wordings will be adapted (only minor changes are required as the Chinese term for “sport” and “physical activity” are the same) to specify need satisfaction towards physical education. A 7-point scale from 1 (*Not true at all*) to 7 (*Very true*) will be used for responses.

#### Autonomous motivation for physical education

Students’ autonomous (eight items; e.g., “because PE is fun”) and controlled motivation (eight items; e.g., “because I’ll get into trouble if I don’t”) towards physical education will be measured using the Chinese version of the Perceived Locus of Causality Questionnaire [49]. Responses will be provided using a 5-point scale from 1 (*strongly disagree*) to 5 (*strongly agree*).

#### Intention to engage in physical activity

Students’ short- and long-term intention to engage in physical activity will be measured using two items (“Do you intend to do physical activity regularly [at least three times a week] during your leisure time in the coming week/three months?”). The Chinese translation of these items will be used. Students will be asked to select “yes” or “no” for both of these questions.

#### Psychological well-being

The Flourishing Scale [50] will be used as a pseudo-measure for students’ psychological well-being. The 8-item scale measures facets of psychological well-being including positive relationships and having meaning and purpose in life (e.g., “I am engaged and interested in my daily activities”). The Chinese translation of the scale will be used in this study. Responses will be made using a 7-point scale from 1 (*strongly disagree*) to 7 (*strongly agree*). The scale was administered to students in a pilot study, and the scale scores had a Cronbach alpha of .92.

#### Health-related fitness

Results from fitness tests used in the Hong Kong School Physical Fitness Award Scheme [51] of students will be collected and used as a measure of health-related fitness. The scheme is government-led, and therefore its test items are applied in most Hong Kong schools. Thus school teachers and students should be familiar with the standardized test items. All test items from the scheme will be used, except the skinfold measurements used as a measure for body composition, as the SELF-FIT was not specifically designed to improve such attributes of students. These include a cardiovascular fitness test (a nine-minute run protocol), one-minute curl up test, sit and reach test, and a push-up test. The test protocols can be accessed from the award scheme website [51].

### Blinding

As teachers will be required to implement the interventions in schools, they will not be blinded to group allocation. Students, however, will not be informed about the group differentiations, and therefore will be blinded to group allocation. Research assistants who are responsible for data collection will not be blinded to group allocation.

### Statistical analyses

The primary outcome to be evaluated in the trial is students’ percentage of time spent in MVPA during school PE. Secondary outcomes include percentage of time spent in leisure time MVPA, perceived need support from teachers, need satisfaction, autonomous motivation, psychological well-being, and intention to engage in physical activity. To account for the clustering nature of data, multilevel analyses will be used. Specifically, for each outcome, a three-level (time within student within class) model will be evaluated. Analyses will be conducted using MLwiN v2.26 [52]. For all outcomes, the effectiveness of the intervention will be examined through the multilevel regression equation:$$ \mathrm{Outcome}=\mathrm{B}0+{\mathrm{Gender}}^{\ast}\mathrm{B}1+{\mathrm{Age}}^{\ast}\mathrm{B}2+{\mathrm{Group}}^{\ast}\mathrm{B}3+{\mathrm{Time}}^{\ast}\mathrm{B}4+{\mathrm{Group}}^{\ast }{\mathrm{Time}}^{\ast}\mathrm{B}5 $$

Specifically, the intervention will be considered to be effective in promoting the outcomes if the Group*Time term is positive and significant at *p* < .05.

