### Sample size calculation

A sample size calculation was completed to estimate the number of schools needed for the trial. The calculation was based on our primary outcome of the percentage of time students spent in MVPA during PE lessons. Based on Lonsdale et al.’s meta-analysis [14], the expected standardized difference, or Cohen’s *d*, between intervention (using fitness infusion strategies) and control groups was 1.4. Using a more conservative estimate, we used *d* = 0.9 for our sample size calculation. Calculations were conducted using GPower 3.1.7, with an alpha level set to .05 and power to .80. The required sample size was calculated to be 42. In the current trial, each class would be treated as an individual cluster. Therefore, the calculated sample size was then multiplied by a design effect of 1 + (*m* – 1)ρ, where *m* represents the cluster size (estimated to be 30) and ρ is the intraclass coefficient (ICC). Based on a study conducted in Hong Kong [17], the ICC was estimated to be at .60. Therefore, the final number of participants required was 42 × [1 + (30-1) × .60] = 773, meaning a total of 26 schools will need to be recruited.

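### The three-level model as described names no class-level Time effect; with intercepts only, the deciding Group × Time test treats students' changes as independent within randomised classes

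*Protocol article*

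**What the plan says.** Under Statistical analyses, the protocol article says that "for each outcome, a three-level (time within student within class) model will be evaluated". The printed equation holds fixed effects only: an intercept, gender, age, Group, Time and Group × Time. No random term or residual is written out. The section gives clustering as the reason for multilevel analysis, applies the same equation to every outcome, and decides effectiveness on Group × Time alone.

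Under Randomization, classes are allocated within matched pairs. With 26 classes this gives 13 per arm.

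Under Outcomes, MVPA in PE is measured "during three randomly selected lessons at each time point", so students of one class are observed in the same few lessons. Under Trial design, baseline and follow-up fall in different halves of the school year.

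Under Sample size calculation, clustering is treated as large: "the calculated sample size was then multiplied by a design effect of 1" + (m − 1)ρ, and "the ICC was estimated to be at .60".

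**The concern.** Group × Time compares the change from baseline to follow-up between arms. Its chance variation has two sources: students changing differently from their classmates, and whole classes moving together. The second matters most here, because the class is the randomised unit.

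Class-wide movement is to be expected for MVPA in PE. Teacher, sport unit and sampled lessons are common to the class, and the two periods lie in different semesters. The three levels named (time, student, class) do not by themselves include a term for it. If none is fitted, the standard error of Group × Time is too small, the confidence interval too narrow and the p-value too low. The trial's primary conclusion rests on that p-value.

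**Working it through.** **Inputs from the protocol (Sample size calculation, Randomization).** Two-group comparison "with an alpha level set to .05 and power to .80"; "we used *d* = 0.9 for our sample size calculation"; cluster size m = 30; ICC = .60; 26 classes, 13 per arm.

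**Inputs not in the protocol, assumed here.** The correlation over time of class effects, r_c, from .50 to 1.00. The correlation over time of student effects within class, r_s, 0.5 with a range of 0.3 to 0.7. One value per student and period (the mean of the three lessons).

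**Step 1: the plan's own figure.** A two-sided two-sample t-test with d = 0.9 needs 21 per arm (power .812), so 42, as stated. The design effect is 1 + 29 × .60 = 18.4; 42 × 18.4 = 772.8, rounded to 773; 773 / 30 = 25.8, so 26 classes. The figures reproduce.

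**Step 2: what cancels.** Write the outcome of student j in class i at time t as fixed effects + c_i + s_ij + (ct)_it + e_ijt. With balanced data, the student's change contains neither c_i nor s_ij. A model with only those two intercepts therefore tests Group × Time as a two-sample comparison of about 780 student changes (26 × 30). Any (ct)_it is absorbed into the residual as if it were independent between classmates.

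**Step 3: size of the error.** The ICC of the change is

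ρ_change = ICC(1 − r_c) / [ICC(1 − r_c) + (1 − ICC)(1 − r_s)].

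The true variance of the contrast exceeds the model's by DE = 1 + (m − 1)ρ_change. The actual two-sided error at nominal 5% is 2[1 − Φ(1.96/√DE)].

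Example, r_c = .95 and r_s = .5: ρ_change = .03 / (.03 + .20) = .130; DE = 1 + 29 × .130 = 4.78; 1.96/√4.78 = 0.896; error = 37%.

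| r_c | ρ_change | DE | Two-sided error | Positive and significant |
|---|---|---|---|---|
| 1.00 | 0 | 1.0 | 5.0% | 2.5% |
| .99 | .029 | 1.84 | 14.9% | 7.4% |
| .95 | .130 | 4.78 | 37.0% | 18.5% |
| .90 | .231 | 7.69 | 48.0% | 24.0% |
| .80 | .375 | 11.87 | 57.0% | 28.5% |
| .50 | .600 | 18.4 | 64.8% | 32.4% |

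The last column applies the protocol's rule that the term must be positive, taking p as two-sided. Varying r_s from 0.3 to 0.7 moves the two-sided error from 12% to 20% at r_c = .99, and from 32% to 45% at r_c = .95. Put directly in terms of the change, ρ_change = .05 gives DE = 2.45 and 21%.

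**Step 4: simulation.** With 26 classes of 30, no true effect and 4,000 replicates per setting, testing student changes as independent rejected in 4.7%, 15.5%, 37.2%, 47.9%, 57.4% and 63.8% for the six values of r_c. Pairing classes on the baseline class mean gave 4.7%, 14.9%, 36.6%, 47.6%, 56.1% and 59.6%, so matching does not repair the test.

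A class-level t-test of change on 24 degrees of freedom rejected in 4.7% to 5.7% without matching and 2.4% to 5.0% with it. With a normal reference in place of t, the unmatched rates were 5.8% to 6.8%.

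A small run with fitted mixed models (12 students per class, 40 replicates, r_c = .90, some convergence warnings) gave 30% for intercepts only and 7.5% with a class-by-time term. It confirms direction only.

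**The case against.** The strongest reply is that the article does not write out the random part at all. Naming the nesting does not exclude a class-level random coefficient for Time, and a condensed article may leave this to an analysis plan that is not shown. That stands: intercepts only is the ordinary reading of the text, not something it states. If a class-level Time effect is already intended, the point reduces to saying so.

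A reader might infer more than the document supports, in four ways:

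- **That the plan ignores clustering.** Class is a level of the model. The difficulty is confined to the Group × Time contrast.
- **That false positives are certain to be frequent.** The inflation depends on a class-by-time variance that the document does not give; at zero the test is valid. Shared lessons make zero unlikely for MVPA in PE, but they do not fix the size.
- **That the two-sided rates are the rates of false claims of benefit.** The sign requirement halves them.
- **That the whole design effect of 18.4 is missing from the test.** That figure belongs to a comparison at one time point. A change contrast properly removes stable class differences; in the table, 18.4 is due only at r_c = .50.

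Nor do the figures carry over to the secondary outcomes. The ICC of .60 is given for MVPA in PE, leisure-time MVPA and the questionnaire constructs are not measures of activity in shared lessons, and the intention items are yes/no.

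**Conclusion.** The point holds in conditional form. If the model is fitted as its description is ordinarily read, the deciding test makes no allowance for class-level change in a trial that randomises classes. For the primary outcome, a class correlation over time of .99 would already roughly triple the two-sided error, and .95 would bring it to about 37%; false claims of benefit would be about 7% and 18% against 2.5% nominal. These figures rest on the protocol's ICC of .60 and class size of 30, an assumed student correlation of 0.5, and lessons averaged within period. The direction is firm whenever class-by-time variance is above zero; the size is not known from the document. Because the primary conclusion hangs on this term, the random part should be settled before analysis.

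**What to change.** State the random part of the model. Alongside the class and student intercepts, include a class-level random coefficient for Time (class-by-time), and a class-by-lesson effect if the three lessons enter as separate rows. Test Group × Time against a t distribution with between-class degrees of freedom: about 24 for 26 classes, fewer if pair-by-time effects are fitted. Pair main effects alone cancel from this contrast, as the class intercepts do.

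Two class-level alternatives are also valid: an analysis of class mean change, or of class follow-up means adjusted for baseline. The latter is a different estimator and leaves about 23 degrees of freedom.

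Use the corresponding class-level Time effect for the other outcomes, with a logistic form for the two yes/no intention items.

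The cost is a sentence or two in the analysis section and no new data. Confidence intervals will be wider to the extent that classes do move between periods.

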### Randomization

Randomization will take place after baseline measures are taken. A matched-pair randomization protocol will be used. Specifically, the classes will be paired based on (1) class sex (mixed versus female versus male), (2) school type (mixed or single-sex), (3) class size (inclusive of non-participating students), (4) average family income (low versus mid versus high; to be reported by school teacher), and (5) the percentage of MVPA during PE measured at baseline. Each class will then be assigned a computer-generated random number. In each matched pair, the class with the larger assigned number will be allocated in the experimental group, while the other class will be assigned to the control group.

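### The success rule for Group*Time is not tied to the 26 randomised classes (13 matched pairs), so its real error rate may sit above or below the nominal 5%

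*Protocol article*

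**What the plan says.** Three sections of the Protocol article bear on this.

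- **Sample size calculation.** One class per school is the cluster, "meaning a total of 26 schools will need to be recruited".
- **Randomization.** Classes are matched on five variables, one of them baseline MVPA in PE. Then "In each matched pair, the class with the larger assigned number will be allocated in the experimental group". That makes 13 pairs.
- **Statistical analyses.** Each outcome gets a three-level model (time, student, class) with fixed effects for gender, age, group, time and Group*Time. "Analyses will be conducted using MLwiN v2.26". The intervention counts as effective if Group*Time has a positive sign and p < .05.

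The section prints no class-by-time random term and no pair term. It names no estimation method, reference distribution or degrees of freedom.

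**The concern.** Treatment is allocated to classes, so the information on Group*Time lies in 26 class-level changes, or 13 pair differences, however many students are measured. With so few units the between-class variance of change is itself poorly estimated. A statistic compared with 1.96 treats that variance as known, and maximum likelihood also estimates it too small. The matching pulls the other way: if paired classes change alike and the analysis ignores this, the standard error is too large.

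At stake is the only success criterion for the primary outcome. A statistic between 1.96 and 2.06 would count as success under one reference and not under the other, and the article does not fix which applies.

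**Working it through.** **1. The plan's own figure.** The inputs are in Sample size calculation: "we used *d* = 0.9 for our sample size calculation", "with an alpha level set to .05 and power to .80", class size 30, and "the ICC was estimated to be at .60".
- A two-sided, two-sample t calculation gives 21 per arm (power 0.812; 20 per arm gives 0.792). The total is 42, as stated.
- Design effect: 1 + 29 × 0.60 = 18.4. Then 42 × 18.4 = 772.8, and 772.8/30 = 25.8, so 26 schools.

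The figure reproduces.

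**2. Class-level statistic with a normal reference.** Assumptions: class-by-time variance is modelled, the cut-off is 1.96, and pairs are ignored. Degrees of freedom: 26 − 2 = 24.
- Restricted estimation: 2·P(t₂₄ > 1.96) = 6.2%.
- Maximum likelihood (variance divisor 26 instead of 24): 2·P(t₂₄ > 1.96·√(24/26)) = 7.2%.
- On the 13 pair differences (12 df): 2·P(t₁₂ > 1.96) = 7.4%, and 2·P(t₁₂ > 1.96·√(12/13)) = 8.4%.
- The matching t critical values are 2.064 (24 df) and 2.179 (12 df).
- Success also needs a positive sign, so a false claim of benefit has half the 24 df rates: 3.1% and 3.6%, against 2.5%.

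Simulation with 13 classes of 30 per arm gives 6.2% and 7.2% when the ICC of change is 0.20. It gives 5.8% and 6.9% at 0.05. At an ICC of zero there is no inflation (4.4% and 4.7%). The document gives no ICC of change, so these values are assumed.

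**3. Matching that works but is ignored.** Simulated two-sided rates (200,000 null trials) over assumed correlations of class change within a pair:

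| Pair correlation | 1.96, restricted | 1.96, ML | t₂₄ | Paired t₁₂ |
|---|---|---|---|---|
| 0 | 6.2% | 7.3% | 5.0% | 5.0% |
| 0.2 | 3.8% | 4.6% | 3.0% | 5.0% |
| 0.4 | 2.0% | 2.5% | 1.5% | 5.0% |

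An exact permutation over the 2¹³ = 8192 within-pair allocations gave 4.9% (4,000 simulated null trials, no pair correlation).

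**4. The equation as printed, with no class-by-time term.** The test then uses student-level variation in change. With 26 × 30 = 780 students and one change each, there are about 778 df, where a normal and a t reference agree (5.04%). If class changes vary, the standard error is too small by √(1 + 29r), with r the ICC of change, and the rate is 2·[1 − Φ(1.96/√(1 + 29r))]:
- r = 0: 5%
- r = 0.01: 8%
- r = 0.05: √2.45 = 1.565, giving 21%
- r = 0.20: √6.8 = 2.608, giving 45%

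Putting 2.064 in place of 1.96 at r = 0.05 gives 2·[1 − Φ(2.064/1.565)] = 18.7%, so a t₂₄ cut-off alone does not repair this model.

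**5. Power on the planning inputs.** This is a follow-up contrast, because no ICC of change is given. Noncentrality: 0.9/√(2 × 18.4/(30 × 13)) = 2.93.
- Cut-off 1.96: 83.0%.
- t on 24 df: 80.3%.
- Paired t on 12 df with no gain from matching: 76.7%. The permutation test simulated at 77%.

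**The case against.** The strongest objection is that this rests on silence. A reader might infer from the software name that the plan prescribes a large-sample Wald test and that this trial's false-positive rate is therefore 6% to 7%. The document does not support that. It names no test, reference or estimation method, and a condensed article commonly leaves such detail to the analysis plan. The 6.2% and 7.2% also belong to a model with a class-by-time term that the printed equation does not show. Matching can reverse the direction of the error. The excess in false claims of benefit is about one percentage point or less.

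All of that stands, and it limits the claim. What remains is that the article does fix the model, the fixed-effects equation and the decision rule, and that this rule as a whole is not linked to the units randomised. A 5% rate results only in particular cases, such as no class-level variation in change, or a suitable class-level reference with no pair correlation. A test built on the randomisation avoids that dependence.

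A reader might also think the remedy is free. It is not: it costs about 3 power points with t₂₄, and about 6 with the within-pair test if matching gains nothing.

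**Conclusion.** The point holds as an inexpensive improvement, not as a demonstrated error. If class-by-time variation is present and modelled, a normal reference is used and pairs are uncorrelated, the two-sided rate is about 6.2% to 7.2%. If pairs are correlated and ignored, the same test is conservative, at roughly 4% (correlation 0.2) or 2% (0.4). If the class-by-time term is absent, the rate depends on an ICC of change that the document does not give and can be far above 7%. The normal reference, the ICC of change and the pair correlation are all assumptions. The documents do not settle which case applies, and that is why the rule should be pinned down.

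**What to change.** In Statistical analyses, before follow-up data are seen, state one of the following for the primary outcome:

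- Group*Time will be estimated by restricted estimation with a class-by-time random effect and referred to t on 24 df. Without that random effect, the t₂₄ cut-off is not enough.
- The primary p-value will come from an exact permutation test of class-level changes over the 8192 within-pair allocations.

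The second follows the actual randomisation and holds its level whether or not the matching works. The first is simpler and keeps planned power at 80.3%, but it becomes conservative if pairs are correlated. The cost is one or two sentences and a short script, slightly wider intervals, and power of 80.3% (t₂₄), or about 77% (within-pair, no matching gain), instead of 83.0%.
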